### Subanalyses

We will further investigate the oxygenator’s function and structure. The former will be done by postoxygenator blood gas sampling, and the latter by oxygenator clot volume assessment by computer tomography scanning. Outcomes by age group (<28 days, 28 to 365 days, and greater than 365 days) will be analyzed.

### Statistical Analysis Plan

#### Analysis Plan

Descriptive statistics will be used to report the baseline characteristics of the total study cohort and each subgroup. The primary efficacy outcome measure investigating days free of ECMO will be analyzed using quantile regression incorporating treatment group and VA or VV support (stratification variable) as fixed effects, with the treatment group effect estimate and 95% CI reported (assuming the data is abnormally distributed). Exploratory subgroup analysis by cardiac, respiratory, and ECMO-assisted cardiopulmonary resuscitation support will be performed. Analysis of secondary outcomes includes comparisons of measurements and proportions, with confidence intervals of differences as the major method of presentation. The primary analysis will be by intention-to-treat. If appropriate, per-protocol analyses will be performed as well and compared to the intention-to-treat. Statistical significance will be set at the .05 level and no adjustment for multiple comparisons will be made, noting the exploratory nature of the analysis. CIs will be generated using quantile regression for abnormally distributed continuous data, a 2-sided *t* test for normally distributed data, and a test of 2 proportions for binary data.

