Nitric oxide (NO) mediates anti-inflammatory host responses and regulates both endothelial functions as well as microvascular inflammation. The mixing of NO into the sweep gas that runs into the oxygenator in neonates and children undergoing cardiopulmonary bypass has been investigated in several pilot studies with promising results, and a large randomized controlled trial (RCT) has recently been published [10-13]. In this trial, the effects of NO used in a bypass circuit for pediatric cardiac surgery were tested [13]. No effect on mortality or on the duration of ventilation was observed, though the safety of NO was high. The treatment duration on cardiopulmonary bypass is a few hours, whereas ECMO support lasts days to weeks, making the 2 clinical scenarios not directly comparable. In addition, mixing NO into the sweep gas (at 30, 50, and 80 ppm) in an animal model of ECMO significantly reduced the host response, with suppression of tumor necrosis factor *α* (TNF-*α*) and interleukin (IL)-6 expression ([name], unpublished data, April 2023). A single-center observational study using historical controls reported the safety and outcomes of NO at 20 ppm mixed into the sweep gas of the ECMO oxygenator. The authors observed a lower blood product administration and a marginal improvement in the survival of patients on NO compared to the historical controls without any NO. There are no randomized studies on the effect of NO mixed into the oxygenator on patients treated with ECMO.

The Nitric Oxide on Extracorporeal Membrane Oxygenation in Neonates and Children (NECTAR) study was designed to investigate in a randomized clinical trial whether mixing NO into the sweep gas in neonates and children treated with ECMO is feasible (recruitment, randomization, and protocol compliance) and safe (accurate NO delivery and methemoglobin levels). Efficacy will be tested by measuring ECMO-free days (the number of days that patients spend alive and free from ECMO is censored at 30 and 90 days) and by assessing the inflammatory host response and coagulation activation. We hereby describe the NECTAR trial protocol.

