**Secondary outcomes**
Survival without extracorporeal membrane oxygenation (ECMO), censored at 30 and 90 days post randomization. Patients dying within 30 and 90 days of presentation will be considered as 0 days, to account for the competing effect of mortality on ECMO-free survival.Survival free of pediatric intensive care unit (PICU; censored at 30 and 90 days)Hospital length of stay post randomizationMedian daily blood product usageComplement system activationChild neurodevelopment, function, and quality of life at 6 and 12 months, as measured by:Ages and Stages Questionnaire (<5 years of age) OR Strength and Difficulties Questionnaire (>5 years of age)Pediatric Quality of Life InventoryPediatric Emotional Distress Scale (2-5 years) OR Children’s Revised Impact of Events Scale (>5 years)Behavior Rating Index of Executive Functioning – Preschool (2-5 years) OR Behavior Rating Index of Executive Functioning – 2 (>5 years)Vineland Adaptive Behavior ScaleParent functioning at 6 and 12 months, as measured by:Parenting Stress Index – Short FormKessler-6Primary Caregiver – Post Traumatic Stress Disorder Scale

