### Secondary Clinical Outcomes

The secondary clinical outcomes include mortality at 30 and 90 days. ECMO-free and PICU-free survival censored at 30 and 90 days post randomization, length of stay at the hospital post randomization, average daily blood product usage, complement system activation with measurements of complement (C)1q, C5a, C9, C3, C4, complement factor B, complement factor H, and Mannose-binding Lectin, as well as neurodevelopmental function and quality of life at 6 and 12 months, will be considered (Textbox 3).

Subanalyses for the Nitric Oxide on Extracorporeal Membrane Oxygenation in Neonates and Children (NECTAR) trial.Cardiac, respiratory, and extracorporeal membrane oxygenation–assisted cardiopulmonary resuscitation outcomes (proportions alive at 30 and 90 days for each group)Circuit duration (time to decannulation or time to circuit change) per treatment groupRenal function measured as creatinine and urine output changes during extracorporeal membrane oxygenation (ECMO) per treatment groupRenal replacement treatment on ECMO (type of renal replacement therapy, duration of slow continuous ultrafiltration, type of filter, and duration of filter viability)Incidence of seizures diagnosed during ECMO or up to 48 hours after decannulationTransmembrane oxygenator pressure assessment every 24 hoursOxygenator clot volume as assessed by the extracorporeal life support assessment monitorOxygenator clot volume (by computer tomography imaging)Hemolysis (plasma-free hemoglobin) per treatment groupMean daily heparin dose per kg required to meet target anticoagulation per treatment group

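### ECMO-free days is primary in the Analysis Plan but secondary in the outcome lists, and its zero-for-death rule is timed from an undefined presentation instead of from randomization

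*Protocol article*

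**What the plan says.** Five places in the protocol article bear on this outcome.

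- **Analysis Plan:** "The primary efficacy outcome measure investigating days free of ECMO" is to be analyzed by quantile regression with treatment group and VA or VV support as fixed effects. No horizon, starting point or death rule is given there.
- **Textbox 1, main study outcomes:** the efficacy entries are inflammation at 1, 12 and 24 hours, coagulation activation and consumption, and clotting and bleeding. ECMO-free days is not among them.
- **Textbox 1, secondary outcomes:** the outcome appears as "Survival without extracorporeal membrane oxygenation (ECMO), censored at 30 and 90 days post randomization". The next sentence gives the death rule: "Patients dying within 30 and 90 days of presentation will be considered as 0 days".
- **Secondary Clinical Outcomes:** the outcome appears again as "ECMO-free and PICU-free survival censored at 30 and 90 days post randomization".
- **Introduction:** "Efficacy will be tested by measuring ECMO-free days", explained in brackets as "the number of days that patients spend alive and free from ECMO is censored at 30 and 90 days", together with the inflammatory response and coagulation activation.

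The Analysis Plan sets significance at .05 without multiplicity adjustment and gives the exploratory nature of the analysis as the reason. Limitations says that the trial is not powered for clinical outcomes such as ECMO-free survival.

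**The concern.** There are two separate faults.

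The first is status. A reader of the Analysis Plan would expect ECMO-free days to lead the efficacy results. A reader of Textbox 1 would expect the biomarkers and the clotting and bleeding events to lead. If the Analysis Plan is followed, it is still unclear whether the 30-day or the 90-day estimate is meant. The label matters in an open-label trial without multiplicity adjustment, because it tells readers which efficacy result was chosen in advance.

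The second is the clock. Two adjacent sentences in Textbox 1 use different starting points for one score. If presentation means something earlier than randomization, such as hospital or PICU admission, the death window closes before the counting window does. Deaths in the gap are then not set to 0, although the stated purpose of the rule is to account for the competing effect of mortality. The Conclusions say that the pilot data will inform a larger trial, so an ambiguous score could carry forward.

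**Working it through.** No figure in the plan depends on this definition. The sample size of 50 rests on a cited recommendation for pilot studies, so there is nothing to reproduce. The check is a comparison of sections followed by scoring examples.

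**Step 1. The sections side by side**

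| Section | Status | Horizon | Time origin | Deaths |
|---|---|---|---|---|
| Introduction | efficacy measure, no rank | 30 and 90 days | not stated | no rule stated |
| Textbox 1, main outcomes | absent | – | – | – |
| Textbox 1, secondary | secondary | 30 and 90 days | randomization | 0 if within 30 and 90 days of presentation |
| Secondary Clinical Outcomes | secondary | 30 and 90 days | randomization | no rule stated |
| Analysis Plan | primary efficacy | not stated | not stated | no rule stated |

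The status column cannot be reconciled as written. The two horizons are given consistently; what is missing is which of them the Analysis Plan means.

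**Step 2. Why the horizon matters if the outcome is primary**

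Take decannulation on day 6 (assumed).

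- Survivor: 30 − 6 = 24 days, or 90 − 6 = 84 days.
- Death on day 60, with the zero rule timed from randomization: 30 − 6 = 24 at the 30-day horizon and 0 at the 90-day horizon.

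**Step 3. The time origin**

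Let d be the day of decannulation and t the day of death, both counted from randomization. Let H be the horizon and L the lag from presentation to randomization. L is an assumption, as the documents give none.

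- Rule timed from randomization: the score is 0 if t ≤ H.
- Rule as written: the score is 0 if t + L ≤ H. Otherwise it is min(t, H) − d, and not below 0.

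The two differ only when H − L < t ≤ H and t > d.

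- L = 5, d = 6, t = 28, H = 30: as written, 28 + 5 = 33 > 30, so the score is 28 − 6 = **22**. From randomization, 28 ≤ 30, so the score is **0**.
- Same patient, H = 90: 33 ≤ 90, so the score is 0 either way.
- L = 5, d = 6, t = 25, H = 30: 25 + 5 = 30 ≤ 30, so the score is 0 either way.
- L = 0: no patient is affected.

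**Step 4. How many deaths could be affected**

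If deaths were spread evenly over the 30 days (assumed), the share falling in the last L days would be L/30: 3/30 = 10%, 5/30 = 17%, 7/30 = 23%, 14/30 = 47%. This is at most an upper bound on the share that escapes the zero. A patient who dies without leaving ECMO has no ECMO-free days and scores about 0 whichever origin is used. Deaths concentrated early in the window would lower the share further.

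**Step 5. The Introduction against Textbox 1**

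With decannulation on day 6 and death on day 25, a literal count of days alive and off ECMO gives 25 − 6 = 19. Textbox 1 gives 0 if presentation is at most 5 days before randomization (25 + 5 = 30). Only Textbox 1 states a rule for deaths, so the Introduction is a loose summary to be aligned with it.

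**The case against.** The strongest defence is that this is a pilot focused on feasibility, safety and exploration of efficacy. It is not powered for ECMO-free survival, and the article condenses fuller documents that are not shown. A SAP may name the lead horizon, and presentation may be a loose word for study entry. All of this stands as a limit on the consequences. It does not make the status labels agree, and it does not define the word used in the death rule.

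Some stronger readings are tempting, but the documents do not support them.

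- **Two competing death rules.** A reader might infer this from the Introduction. Its bracketed phrase says nothing about patients who later die, and Textbox 1 holds the only explicit rule.
- **Two horizons as an error.** Reporting both is legitimate. The gap is only that the outcome called primary has no stated lead horizon.
- **An inflated false-positive rate.** A simulation with no true effect and 25 per arm put the chance of at least one p < .05 among four versions (two horizons by two death rules) at about 0.086 to 0.088, against 0.044 to 0.048 for each version alone. It assumes ECMO durations and mortality, uses rank-sum tests in place of quantile regression, and counts the Introduction's phrase as a second rule. It therefore does not measure the point made here.
- **A choice left open until the data are seen.** The trial is registered, and neither the registry record nor a SAP is at hand. The text permits the ambiguity but does not show that it was left unresolved.
- **The lag shares as the proportion of deaths misclassified.** They rest on assumed lags and evenly spread deaths, and they ignore deaths on ECMO.

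**Conclusion.** The point holds in two parts. The Analysis Plan's primary label contradicts Textbox 1 and Secondary Clinical Outcomes, and it comes without a horizon. Within Textbox 1, the counting window and the zero-for-death window start from different events, one of them undefined.

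For a single patient the second fault can be large (22 days against 0 in the example). Across the trial its size is unknown: it depends on what presentation means, on the lag, and on how many deaths follow decannulation within the window. If presentation and randomization coincide, it vanishes. The severity is moderate, because the efficacy analysis is exploratory and unpowered for this outcome, and the sample size does not rest on it.

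**What to change.** 1. Give the outcome one status in Textbox 1, Secondary Clinical Outcomes and the Analysis Plan. Either delete the word primary in the Analysis Plan, which is the smaller change, or list ECMO-free days in Textbox 1 as the primary efficacy outcome and name one lead horizon. The documents do not decide between these routes, or between day 30 and day 90.
2. In the Textbox 1 death rule, replace presentation by randomization. Specify the first randomization, because Randomization and Blinding provides that a patient is randomized again for a second ECMO run.
3. Align the Introduction's bracketed definition with the zero-for-death rule.

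The cost is a wording change in the protocol, carried into any SAP, before analysis. It needs no new data and leaves the sample size unchanged.

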### Data Collection, Management, and Analysis

#### Data Collection

Baseline variables (demographics, primary diagnosis, comorbidities including syndromes), precannulation disease severity, precannulation surgery (such as cardiac surgery), cannulation technique, primary and secondary end points, as well as predetermined physiological variables of interest, will be recorded and entered prospectively into a purpose-built REDCap database [14,15]. Treatment that is administered continuously (such as heparin or inotropes) will be recorded as maximal values that were maintained for at least 4 hours. Physiological and blood parameters will be recorded precannulation, at 1, 12, and 24 hours post cannulation, and daily thereafter. The duration of circulatory, renal, and ventilatory support on and off ECMO will be recorded. Gross functional performance assessment will be recorded upon admission to the PICU and upon discharge from the hospital [18].

Participant data confidentiality will be ensured by the study coordinator, the research staff, and the institution sponsoring the trial. All data, as well as the study protocol and any other information that this trial may generate, will be held in strict confidence.

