### Efficacy Outcomes

Host inflammation and complement components will be assessed before cannulation and at 1, 12, and 24 hours post cannulation by determining serum concentrations of C-reactive protein, procalcitonin, IL-1b, IL-6, IL-8, IL-10, and TNF-*α*. At the same time points, coagulation system activation will be assessed by measuring the international normalized ratio (INR), prothrombin time (PT), activated partial thromboplastin time (APTT), thromboelastography (TEG), antithrombin, soluble CD40L, P-selectin, platelet factor 4 levels, and ADAMTS13 release (see Textbox 2). A single measurement of Von Willebrand factor at initiation followed by daily measurements will be performed. After the initial 24 hours, further daily laboratory testing will include D-Dimers, TEG, INR, PT, APTT, anti Xa and activated clotting time (by TEG), and plasma-free hemoglobin. Clotting and bleeding complications and the rate of clotting and bleeding events will be measured. Clotting events are defined as the need to change ECMO circuit componentry due to high transmembrane pressures, high D-Dimers, or high free plasma hemoglobin. Bleeding rates will be measured by both the amount of bleeding per day as well as the daily requirement for blood product administration.

Coagulation, inflammation, and complement system measurements.Coagulation system measurementsChange in granule (soluble CD40 ligand and P-selectin) and chemokine (platelet factor 4) levels released by activated plateletsADAMTS13 releaseChange in van Willebrand factor concentrations during and after the extracorporeal membrane oxygenation (ECMO) runChanges in inflammatory and complement system activationChange in C-reactive protein, procalcitonin, interleukin (IL)-1b, IL-6, IL-8, IL-10, and tumor necrosis factor *α* (inflammatory mediators) levels; Complement (C)1q, Complement Factor B, Complement Factor H, C5a, C9, and Mannose-Binding Lectin (classic and alternate complement pathways); and C3, C3 and CH50.

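### The Analysis Plan names only two-group methods for independent observations and does not say how each child's serial marker values, or the pre-cannulation value, enter the comparison

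*Protocol article*

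**What the plan says.** The Analysis Plan section of the protocol article sets out one model in full. This is a quantile regression of days free of ECMO on treatment group and VA/VV support, an outcome with one value per run. For the remaining outcomes it gives a rule by data type. Skewed outcomes come first: "CIs will be generated using quantile regression for abnormally distributed continuous data". Outcomes that look normal get a two-sided t test, and binary outcomes get a comparison of two proportions. It calls the analysis exploratory, makes confidence intervals of differences the main form of presentation, and does not adjust for multiplicity.

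Textbox 1 lists systemic inflammation and coagulation activation among the main efficacy outcomes. Efficacy Outcomes gives the schedule for the inflammatory markers: "Host inflammation and complement components will be assessed before cannulation and at 1, 12, and 24 hours post cannulation". The coagulation markers share those four sampling times. A subset goes on for longer: "After the initial 24 hours, further daily laboratory testing will include D-Dimers, TEG, INR, PT, APTT, anti Xa". Activated clotting time and plasma-free hemoglobin belong to the same daily list, and von Willebrand factor is also measured daily. Textbox 2 describes many of the markers as a change, without saying between which times.

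**The concern.** The child is the unit of randomization, but each marker yields a pre-cannulation value and three later values per child, and some measures yield many more. In standard form, each named method expects one independent value per child. The step from several values to one comparison is not stated for these markers, and the possible readings differ in quality:

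- **Separate test at each time.** This is valid, but each test ignores the child's other samples and the baseline. It gives three correlated answers per marker and no overall estimate.
- **Daily tests late in the run.** These compare only children still alive and on ECMO that day. That group is formed after randomization and may itself depend on treatment.
- **One summary per child.** This is sound, but it is not named for these markers.
- **All rows in one test.** This is invalid, because repeated values would count as separate children.

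The markers are the pilot's proxy evidence of efficacy, and the Conclusions say that the data will inform a definitive trial. With about 25 children per arm, precision is scarce.

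**Working it through.** **Inputs from the protocol.** 50 patients, allocated 1:1, so 25 per arm; two-sided 0.05; one pre-cannulation and three post-cannulation samples. The protocol gives no SD, numeric effect size, power or within-child correlation for any marker, so there is no figure of its own to reproduce.

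**Assumptions.** Standardized effect d = 0.5, the same at all three times; equal correlation ρ among all four samples, 0.3 to 0.7; normal data after any transformation; no missing samples; one run per child. The medium effect in Sample Size refers to the later main trial's outcome, so d = 0.5 is illustrative only.

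**Step 1: variance of the between-arm contrast, relative to one time point (= 1).**
- Mean of three samples: (1 + 2ρ)/3
- One time point adjusted for baseline: 1 − ρ²
- Mean of three adjusted for baseline: (1 + 2ρ)/3 − ρ²

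**Step 2: power** = Φ(d / √(2V/25) − 1.96), with V from step 1. For V = 1: 0.5/0.2828 = 1.768, and Φ(−0.192) = 0.42.

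| ρ | One time point | One time point + baseline | Mean of 3 | Mean of 3 + baseline |
|---|---|---|---|---|
| 0.3 | 0.42 | 0.46 | 0.68 | 0.76 |
| 0.5 | 0.42 | 0.53 | 0.58 | 0.78 |
| 0.7 | 0.42 | 0.70 | 0.51 | 0.89 |

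Simulated t tests (20,000 trials) gave slightly lower values: 0.40 to 0.41 for one time point, and 0.66, 0.57 and 0.48 for the mean of three. Averaging helps most when correlation is low, and baseline adjustment when it is high.

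**Step 3: the same gain as interval width** (√V, relative to one time point). Mean of three: √0.533 = 0.73, √0.667 = 0.82, √0.8 = 0.89. With baseline: √0.443 = 0.67, √0.417 = 0.65, √0.31 = 0.56.

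**Step 4: error rate of separate tests.** Each simulated test held 0.049 to 0.053. The chance of at least one false positive over the three times, for one marker, was 0.11 to 0.14.

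**Step 5: pooled rows, as a hypothetical.** Design effect 1 + (3 − 1)ρ = 1.6, 2.0, 2.4. Type I error = 2[1 − Φ(1.96/√design effect)] = 0.12, 0.17, 0.21; simulation gave 0.125, 0.165, 0.212. Intervals would have 1/√1.6 = 0.79, 0.71 and 0.65 of their proper width.

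**The case against.** The strongest reply is that the protocol makes no error here. Nothing in it says that rows will be stacked. Textbox 1 lists inflammation at three named hours, which reads naturally as a comparison at each. Textbox 2 speaks of change, which is a per-child score. Blood products and heparin are already described as per-day averages or medians. The named tests suit any such single value. The analysis is declared exploratory, multiplicity is openly accepted, and no power is claimed. The article is also condensed, and a fuller plan may specify a repeated-measures model.

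Most of this stands. A reader might infer that the plan will produce inflated false-positive rates, but the text does not support that; inflation is only what would follow if someone pooled. A reader might also take the general recording schedule in Data Collection, "at 1, 12, and 24 hours post cannulation, and daily thereafter", to mean that the cytokines are serial for the whole run. Biobanking and Efficacy Outcomes schedule them only up to 24 hours. Nor is ECMO-free days the only outcome that fits the named methods: mortality, hospital stay and mean daily heparin dose also give one value per child.

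What the reply does not remove is that methods are written down here, by data type, and the per-child step for the main markers is not. The absence of a power claim does not settle the matter either. The section makes confidence intervals its main product, and step 3 shows that they can be narrower at no cost in patients or samples.

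**Conclusion.** The point holds as one of efficiency and clarity. The named methods are valid at each time point but make poor use of the samples collected, and comparisons late in the run are conditional on still being alive and on ECMO. Under the stated assumptions, power at d = 0.5 rises from about 42% to 51% to 68% with the three-sample mean, and to 76% to 89% with the pre-cannulation value as well. The baseline gain assumes that the pre-cannulation sample correlates with later samples as strongly as they do with each other; if it correlates less, the gain shrinks. An effect that is not constant over time would also reduce the gain from averaging.

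The type I error of 12% to 21% describes pooling, which the protocol does not propose, and should not be read as a property of the plan. The days-free-of-ECMO analysis is not affected.

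**What to change.** In the Analysis Plan:

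- Keep the named tests for outcomes with one value per child.
- For the 1, 12 and 24 hour markers, fit one repeated-measures model per marker, on the log scale where skewed. Include arm, time, arm-by-time, the pre-cannulation value and VA/VV stratum, and allow for within-child correlation. Report the contrast averaged over the post-cannulation samples, with the time-specific contrasts beside it.
- For daily measures, use one summary per child over a fixed early window, the same in both arms, or a mixed model with child as the cluster. Do not pool rows. Describe results for later days as conditional on still being on ECMO, because neither approach by itself removes that selection.

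The cost is a few lines of text and some programming, with no new patients or samples. The averaged contrast is less sensitive to an effect confined to one time point, which the time-specific contrasts would still show. On the log scale the result is a ratio of geometric means rather than a difference in medians.

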### Randomization and Blinding

Treatment group allocation will be performed using a web-based REDCap electronic data capture tool hosted by The University of Queensland [14,15]. A randomization sequence using variable block randomization with a 1:1 ratio was uploaded into REDCap prior to the screening of the first patient. Randomization is stratified by veno-arterial (VA) versus veno-venous (VV) support. Where conversion of VV to VA or VA to VV occurs, patients will remain in the initial randomization allocation and strata. When a second ECMO run is commenced, the patient will be randomized again.

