### Sample Size

The NECTAR trial is a pilot RCT with the main focus on feasibility, safety, and exploration of efficacy. A sample size of 50 patients has been chosen in line with the recommendations for pilot studies that anticipate a medium effect size for a continuous primary outcome for the main trial [17].

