#### Biobanking

Blood samples for inflammatory and coagulation pathway activation will be collected prior to cannulation, as well as at 1, 12, and 24 hours post commencement of ECMO. These samples will be frozen using standard operating procedures and batch tested.

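### Only ECMO-free days is adjusted for the VA/VV stratum; the t test and two-proportion test named for other outcomes can use neither the stratum nor the pre-cannulation marker value, which costs precision with 25 per arm

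*Protocol article*

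**What the plan says.** **Design.** The Randomization and Blinding section states: "Randomization is stratified by veno-arterial (VA) versus veno-venous (VV) support". Allocation is 1:1 in variable blocks, and the total is 50 children.

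**Analysis.** The Analysis Plan gives one outcome, ECMO-free days, a model with treatment and VA/VV as fixed effects (quantile regression). For other outcomes it speaks of comparing measurements and proportions, and it assigns methods by data type: "CIs will be generated using quantile regression for abnormally distributed continuous data", a two-sided t test for normal data, and a two-proportion test for binary data. It names no covariate for any of these. It adds: "Statistical significance will be set at the .05 level and no adjustment for multiple comparisons will be made".

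**Baseline.** Under Biobanking: "Blood samples for inflammatory and coagulation pathway activation will be collected prior to cannulation", with further samples at 1, 12 and 24 hours. Under Efficacy Outcomes: "Host inflammation and complement components will be assessed before cannulation and at 1, 12, and 24 hours post cannulation". The coagulation markers follow the same times, except Von Willebrand factor, which is measured at initiation and then daily.

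**Form of the outcome.** Textbox 1 lists systemic inflammation as levels at the three follow-up times. Textbox 2 describes the inflammatory mediators and platelet-release markers as change.

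**The concern.** Inflammation and coagulation activation are main efficacy outcomes of this pilot, and its data are meant to inform a definitive trial. Children from birth to 16 years are eligible, and presentations range from respiratory failure to cardiac arrest, so marker values before cannulation may differ widely between children. The Limitations section itself expects that risk factors may not balance between the arms.

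NO is delivered through the oxygenator, so treatment cannot affect a sample drawn before cannulation. That makes it a sound covariate. A t test on follow-up values ignores it. A t test on change uses it by subtraction, which is less efficient than regression and, when the correlation is low, worse than ignoring it. Because levels versus change is not settled, the reader cannot tell which loss applies.

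The plan is also uneven: it accepts adjustment for the stratification factor for one outcome and names tests that rule it out for others. At stake is the width of the confidence intervals, which the Analysis Plan makes its main form of presentation.

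**Working it through.** **The plan's own figure.** The Sample Size section gives this basis for the total: "A sample size of 50 patients has been chosen in line with the recommendations for pilot studies". It describes the effect expected in the main trial only as medium. No power, SD or numeric effect is given, so 50 can be neither reproduced nor refuted by a power calculation. For orientation, a standardised difference of 0.5 (an assumed reading of medium) would need 2 × (1.960 + 0.842)² / 0.5² = 62.8, or 63 per arm, at 80% power. The check below therefore concerns precision at 25 per arm.

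**Inputs.** From the article: 50 children at 1:1, so n = 25 per arm; two-sided 0.05. Assumed, because the article gives neither: the correlation r between pre-cannulation and follow-up value (range 0.1 to 0.7), and equal SDs at both times on the analysis scale.

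**Formulas, in SD units.**
- Follow-up value only: half-width of the 95% CI = 1.96 × √(2/25) = 0.554.
- Change score: 0.554 × √(2(1 − r)).
- Baseline-adjusted: 0.554 × √(1 − r²).
- SE ratio, adjusted to follow-up only: √(1 − r²). Adjusted to change: √((1 + r)/2).
- Effective n per arm relative to follow-up only: 25/(1 − r²).

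| r | Follow-up only | Change | Adjusted | SE cut vs follow-up | SE cut vs change | Effective n per arm |
|---|---|---|---|---|---|---|
| 0.3 | 0.554 | 0.656 | 0.529 | 5% | 19% | 27.5 |
| 0.5 | 0.554 | 0.554 | 0.480 | 13% | 13% | 33.3 |
| 0.7 | 0.554 | 0.429 | 0.396 | 29% | 8% | 49.0 |

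At r = 0.3 the change score gives an interval 18% wider than ignoring baseline (0.656/0.554 = 1.18).

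**Low correlations.** √(1 − 0.1²) = 0.995 and √(1 − 0.2²) = 0.980, so the gain over follow-up only is 0.5% and 2%. Estimating one more coefficient costs a factor of about √(46/45) = 1.011. This cancels the gain at r = 0.1 (0.995 × 1.011 = 1.006) and trims it slightly at r = 0.5 (0.866 × 1.011 = 0.876, a 12% cut).

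**Detectable effect at r = 0.5.** With 80% power and the t distribution, 0.81 SD falls to 0.809 × √0.75 = 0.70 SD. By the normal approximation, (1.960 + 0.842) × √(2/25) = 0.79 falls to 0.79 × 0.866 = 0.69.

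**Stratum.** Let q be the share on VV and D the VA–VV difference in within-stratum SDs, both assumed. Then R² = q(1 − q)D² / (1 + q(1 − q)D²) and the SE ratio is √(1 − R²).
- q = 0.2, D = 0.5: R² = 0.04/1.04 = 0.038, ratio 0.981.
- q = 0.5, D = 0.5: R² = 0.0625/1.0625 = 0.059, ratio 0.970.
- Over q from 0.1 to 0.5 and D from 0.3 to 1.0: ratio 0.996 to 0.894.

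Adjusting for VA/VV alone is thus worth about 2–3% in typical cases and 0.4% to 11% over the whole range.

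**The case against.** The strongest reply is that this is a condensed article about an exploratory pilot, declared not powered for clinical outcomes, and that covariates, transformations and repeated-measures models are commonly left to a statistical analysis plan, which is not shown here. That stands for the quantile regressions: the method takes covariates, the same paragraph uses it with VA/VV, and silence elsewhere is not a prohibition. Skewed markers may well go down that route. It does not stand for the t test and the two-proportion test, which are named and have no place for a covariate.

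A reader might infer four stronger things that the article does not support.
- **That the pre-cannulation sample is discarded.** Textbox 2 speaks of change, which uses baseline by subtraction.
- **That each time point is tested separately, so that one marker could be a mean difference at 1 hour and a median difference at 24 hours.** The article does not say how the time points are combined.
- **That the results would be biased.** Under randomisation, chance imbalance is already reflected in an unadjusted interval.
- **That the baseline argument covers every outcome.** Deaths, lengths of stay and event counts have no pre-cannulation value; only the stratum is available for them.

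It is also fair to say that the gains rest on assumed correlations and on comparisons of means, so they do not describe quantile regression. Correlations could be low, because the start of ECMO is itself a large new insult.

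**Conclusion.** The point holds as one of efficiency and consistency. Two of the three methods named for outcomes other than ECMO-free days cannot use the stratification factor or the pre-cannulation value; the third is left open; and the markers are called levels in Textbox 1 and change in Textbox 2.

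For mean-based analyses of the markers, the avoidable loss is material if the correlation is about 0.5 or more, modest at 0.3 against follow-up values, and negligible at 0.1 to 0.2. Against change scores the order reverses, with the largest loss at low correlation. The stratum matters less for width than for agreement between analysis and design. The article gives no correlation, VV share or VA–VV difference, so the size cannot be pinned down. The unadjusted analyses are valid, and the exploratory aim limits the harm; but with 25 per arm, precision that is already paid for in collected samples is worth keeping.

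**What to change.** - **Markers.** Analyse each inflammatory, complement and coagulation marker by regression on treatment, pre-cannulation value and VA/VV, with a log scale fixed in advance where skew is expected. A longitudinal model with a constrained common baseline and treatment-by-time terms is one suitable form. It keeps children without a pre-cannulation sample, which emergency cannulation may produce, under a missing-at-random assumption that should be stated.
- **Effect measure.** Report one measure for each marker at 1, 12 and 24 hours, such as the ratio of geometric means with its 95% CI, rather than letting the observed distribution choose between a mean and a median difference. Reconcile Textboxes 1 and 2 accordingly. Name the baseline for Von Willebrand factor, which has its own schedule.
- **Other continuous outcomes.** Include VA/VV in the regression, and say so for the quantile regressions.
- **Binary outcomes.** Replace the two-proportion test by a stratum-adjusted risk difference, for example Mantel-Haenszel.

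The cost is revised wording, modest extra programming and a transformation chosen beforehand. No new data are needed.
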